
Subjects in the treatment group will receive CM granules in dosages equivalent to the decocting piece dosages shown above according to the IMP manufacturer’s illustration (estimated granule weight per dose: 33.4–59.7 g), and will be dissolved in hot water and administered while it is warm. Participants will take 1 dose a day, and the medication will be divided into two portions, with one in the morning and the other in the evening after meal. The time of treatment and medication is 14 days at maximum or until patients get negative RAT results on two successive days and the major symptoms subside (define as oral temperature ≤37.2°C, the score of cough and fatigue ≤1). The actual duration is determined by the patient according to their own condition, and they can also seek advice from the research team or registered CMPs though the direct phone line if necessary.

The CM granules are planned to be a mixture of single granules produced by PuraPharm, a commercial company in Hong Kong. Most of these granules are made from botanical drugs used in CM, with some made from fungi (*Lasiosphaera Calvatia, Poria*), animal (*Margaritifera Concha*), and mineral (*Gypsum Fibrosum*). They are turned into granules by using modern methods that mimic the old way of making CM decoction. PuraPharm is the main provider of these granules to Hong Kong’s hospitals and health institutions. The botanical, animal and mineral drugs meet the standards of Chinese Pharmacopoeia if they are included. This company follows the GMP standards of the PRC, Australia and the US for quality control and production. It also has an ISO 17025 certified laboratory to check the quality.

The placebo was made from Sorbitol, Maltodextrin, Corn Starch, Soluble Fiber, Black Bean Extract, Abelmoschus esculentus Extract, Green Tea Extract, Caramel Color Powder, Citric Acid and Ginseng Flavo, whose appearance, smell and taste was similar to the CM granules. Subjects will be instructed to take them in the same way as in the treatment group. Each study subject will be given relevant information on the use and storage of IMPs. The granules of both treatment and placebo group will be produced by a manufacturer with a GMP certificate.

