### Study outcomes

#### Assessment

1. The time between starting medication and body temperature returning to normal and the recurrence rate of fever after momentary recovery. Each subject will be issued with the same type of oral thermometer for measurement at 9 a.m. (±2 h) and 9 p.m. (±2 h) daily, with at least 12 h between each measurement. Normal oral temperature is defined as equal to or below 37.2°C. Temperature recovery time is defined as the total number of days between medication starting date and the date of “normal oral temperature for 24 h without antipyretic” (both days inclusive). Subjects are required to measure the temperature until day 14 or on the day when the temperature has remained normal for 24 h, whichever is later.2. The negative rate of RATs at day 14 and negative conversion time. Each subject will be issued with the same type of RAT kits which can be used for at least 14 days for testing at 9 a.m. (±2 h) each day, with at least 24 h between each test. Negative conversion time is defined as the total number of days between the medication starting date and the date of securing two successive negative RAT results (both days inclusive). Subjects were required to undergo testing until day 14 or the day when two successive negative RAT results at least 24 h apart are obtained, whichever is later.3. The remission rate at day 14 and remission time of major symptoms.4. The disappearance rates at day 14 and disappearance time of symptoms. Subjects are required to record the status of their symptoms including major clinical symptoms daily at 9 p.m. (±2 h). Except for fever which is marked as ‘No’ or ‘Yes’ according to whether the oral temperature exceeds 37.2°C, other symptoms will be graded on a scale of 0–4 from “None”, “Mild”, “Moderate”, “Severe” and “Very Severe” depending on the actual feelings of the subject (“None” means the symptom is not present, “Mild” means the symptom is present but does not interfere with daily activities; “Moderate” means the symptom is present and slightly interferes with daily activities; “Severe” means the symptom is present and most daily activities cannot be done; “Very Severe” means the symptom is present and interferes with all daily activities). Major clinical symptoms include fever, cough and fatigue. Remission is defined as oral temperature ≤37.2°C, cough and fatigue score ≤1; disappearance is defined as the symptom being present at day 0 (score >0) but the symptom score is 0 at the date of recording.5. All-cause mortality at the 21st day after stopping the medication.6. Incidence of the progression to severe or critical illness during the trial. The all-cause mortality at the 21st day after stopping the medication and the incidence of the progression to severe or critical illness during the trial will be confirmed by communication with the subjects and/or other related person(s) or checking their medical record in the Hospital Authority. The definitions of severe and critical illness are based on the related definitions of “Coronavirus disease 2019 (COVID-19) Treatment Guidelines” published by National Institutes of Health (severe illness: oxygen saturation in the indoor environment of sea level <94%, oxygenation index [PaO2/FiO2] < 300 mmHg, respiratory frequency >30 breaths/min, lung infiltrates >50%; critical illness: respiratory failure, septic shock, and/or multiorgan dysfunction or failure).7. Utilization rates of antipyretic, Paxlovid and molnupiravir within 14 days and the total dosage(s) of the drug(s) used. In this study, subjects are allowed to take western medicines prescribed for the treatment of COVID-19 under the current guidelines of the Hong Kong Hospital Authority with at least 2 h’ gap between Chinese and western medicines. If oral temperature >39.0°C and continues over 4 h; or the oral temperature >39.5°C, the patient is advised to take antipyretic (paracetamol is recommended as a priority) for acute treatment. Patients need to record the amount and time of the drug(s) used.8. Oxygen saturation. For safety reasons, each subject will be issued with the same type of pulse oximeter for measurement at 9 a.m. (±2 h) and 9 p.m. (±2 h) daily, or whenever the subject decides it is necessary. If the reading is less than 94%, the patient is considered to have severe illness and has reached the end point of the study and is recommended to seek medical attention immediately. Subjects are required to measure their oxygen saturation at rest until day 14 or the time of body temperature returning to normal (continuing for 24 h) or the negative conversion time (2 successive negative RAT results), whichever is later.

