#### Statistical analysis

Basic demographic data (gender, age, *etc.*) will be descriptively summarized. Continuous variables are presented as mean ± standard deviation (SD) and categorical variables are presented as ratios. Intra group comparisons between baseline and each visit will be conducted by using paired *t*-test (or Wilcoxon signed rank test). Linear mixed model will be used to compare the outcomes between groups. All statistical tests will be two-sided, and *p* < 0.05 is considered significant difference. The statistical analysis will be done by an independent statistician and all analysis will be conducted by SPSS. If there is a significant difference in the use of western medicines between the treatment and control groups, it will be considered and processed as a covariance in the statistical analysis.

In this study, the subject will be deemed as “per protocol” if they have taken the maximum dose or if they stop until getting negative RAT results on two successive days and the major symptoms subside (defined as oral temperature ≤37.2°C, the score of cough and fatigue ≤1) with ≥85% intake compliance. The intake compliance is calculated by dividing the no. of packs of drugs ingested by either:a) the number of packs of core formula the subject should take daily (daily dose) x the number of days from the day of starting drug intake to the day the drug is stopped according to the criteria (e.g., if the subject should take 4 packs of core formula a day, starts taking drug on 1 January, stops at 8 January according to criteria, and has taken 30 packs, the compliance will be (30/(4 × 8)) x 100%) = 93.75%, with the subject deemed as “per protocol”; orb) daily dose x 14 for all other cases (e.g., if the subject should take 4 packs of core formula a day, starts taking drug in 1 January and stops at 3 January because of adverse events, and has taken 12 packs, the compliance will be (12/(4 × 14)) x 100%) = 21.43%, with subject deemed as not “per protocol”.

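### Case (a) of the compliance formula charges whole days at both ends of treatment, so a fully adherent subject with a short course and a partial first or last day can score below 85%

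*Protocol article*

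**What the plan says.** The Statistical analysis section classes a subject as per protocol if the maximum dose was taken, or if the subject stopped under the recovery criteria "with ≥85% intake compliance". In case (a), for subjects who stop under the criteria, the denominator is the daily number of core-formula packs times "the number of days from the day of starting drug intake to the day the drug is stopped according to the criteria". The example reads "if the subject should take 4 packs of core formula a day, starts taking drug on 1 January", then "stops at 8 January according to criteria, and has taken 30 packs, the compliance will be (30/(4 × 8)) x 100%) = 93.75" per cent. Case (b), for everyone else, uses a fixed 14 days.

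The Study medications section says that "the medication will be divided into two portions, with one in the morning and the other in the evening after meal". Treatment runs for at most 14 days or "until patients get negative RAT results on two successive days and the major symptoms subside". It adds: "The actual duration is determined by the patient according to their own condition". No minimum course length is given.

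The Baseline randomization section has the product sent by delivery service, with no time of day fixed for the first portion. In the Assessment section, RAT kits are "for testing at 9 a.m. (±2 h) each day, with at least 24 h between each test". The same section has temperature taken at about 9 a.m. and 9 p.m., and symptoms scored at about 9 p.m.

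**The concern.** The denominator works in whole calendar dates, while intake works in half days. If the first portion is an evening one, the morning portion of that date was never due, yet it is charged. If the subject stops after a morning portion, the evening portion of that date is charged in the same way. The formula cannot tell a portion that was not due from one that was missed.

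The charge is a fixed number of portions, so it weighs most on short courses. In case (a) the course length is set by two negative RAT days together with settled symptoms. These are close to two secondary outcomes, negative conversion time and time to remission of major symptoms. Membership of the per-protocol set would then depend partly on how fast a subject recovers after randomisation, for a reason unrelated to adherence. A subject with a short course cannot qualify through the maximum-dose route instead. Reported compliance would also be too low.

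**Working it through.** **Inputs.** Threshold 85%, the case (a) denominator and both worked examples: Statistical analysis. Two portions a day: Study medications. Assumption: the two portions are equal, so two packs each in the 4-pack example.

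**Step 1. Reproduce the article's figures.** Case (a): 30/(4 × 8) = 30/32 = 93.75%. Case (b): 12/(4 × 14) = 12/56 = 21.43%. Both agree. Leaving out one end date in case (a) would give 30/(4 × 7) = 30/28 = 107.1%, so the example does charge both end dates in full.

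**Step 2. What the examples imply about the stop date.** In case (a), seven dates at 4 packs allow at most 28 packs, so a subject who took 30 must have taken some on 8 January. In case (b), 12 packs at 4 a day fill 1, 2 and 3 January completely. In both examples the stop date is therefore consistent with a day of intake. On that reading at most two portions can be not due: the morning one on the first date and the evening one on the last.

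**Step 3. Score of a subject who misses nothing that was due.** Over N inclusive dates, 2N portions are charged. If s of them were not due, the score is (2N − s)/2N.

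| N dates | s = 0 | s = 1 | s = 2 |
|---|---|---|---|
| 2 | 100% | 75.0% | 50.0% |
| 3 | 100% | 83.3% | 66.7% |
| 4 | 100% | 87.5% | 75.0% |
| 5 | 100% | 90.0% | 80.0% |
| 6 | 100% | 91.7% | 83.3% |
| 7 | 100% | 92.9% | 85.7% |
| 8 | 100% | 93.75% | 87.5% |

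With one portion not due, the subject fails up to N = 3 and passes from N = 4. With two, the subject fails up to N = 6 and passes from N = 7.

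**Step 4. The article's own example again.** 30 of 32 packs is one two-pack portion short. That is the score either of a subject who missed a portion or of one who missed nothing and began in the evening. The ambiguity does no harm there, because an 8-date course absorbs it.

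**Step 5. Effect of counting portions due.** With the denominator 2N − s, the same subject scores 100% at every N. A real omission still counts: with N = 3 and s = 1, five portions are due, and missing one gives 4/5 = 80%.

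**The case against.** Several objections are sound and limit the point.

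- A reader might add a third lost portion: an evening start, then a stop on a date when nothing was taken. That would extend failure to N = 9, since (18 − 3)/18 = 83.3%, and would put a perfect adherer on an 8-date course at (16 − 3)/16 = 81.25%. The documents do not support it. In both worked examples the stop date fits a day of intake, and the 8-day example itself passes at 93.75%.
- A reader might infer that evening starts are usual because the product is delivered. The article gives no delivery time or time of first intake, and Table 1 allows screening the day before medication begins.
- A reader might infer from the 9 a.m. RAT that stopping normally happens in the morning. The criterion also needs temperature and symptom scores, and symptoms are scored at about 9 p.m. Where same-day scores are used, the stop is an evening one and the last date loses nothing.
- Failing with one lost portion requires two negative RAT days and settled symptoms within three dates of first intake, in subjects who were febrile at screening. That may be rare.
- The article ties no analysis to the per-protocol set. Uneven loss between arms would arise only if the granules shorten the course. Losing fast treated responders would then tend to weaken a per-protocol effect, not create one.

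It can also be said that half-day counting is a detail for the full protocol or SAP. That does not stand here, because the article itself fixes the formula, the threshold and the day count by example. The rule as written misclassifies some adherent subjects.

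**Conclusion.** The point holds as a defect in a stated rule, of optional to low priority. A subject who takes every portion due can be classed as not per protocol when the course covers at most 3 dates with one end portion not due, or at most 6 dates with two not due. A morning start with an evening stop is scored correctly at any length.

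This rests on equal portions, on both end dates being charged as in the worked example, and on the stop date being a day of intake. The article gives neither the spread of course lengths nor the times of first and last intake. The number affected is therefore unknown and could be negligible.

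The consequence is confined to per-protocol membership, which would depend partly on speed of recovery, and to reported compliance, which would be understated. A reader might infer that the primary result is biased. The article does not support that, because it does not link the primary analysis to this set.

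**What to change.** In case (a), replace the product of daily packs and calendar days with the number of packs due, counted in half-day portions. Count from the first portion taken through the last portion due before the subject actually stopped under the criteria. The count should run to the actual stop, not to the moment the criteria were first met. Subjects decide their own duration, and some may continue past that moment, which would otherwise push their score above 100%. Keep the 85% threshold and leave case (b) as it is. Dosing and stopping rules are not touched.

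The cost is one sentence in the per-protocol definition, and a daily intake record that shows morning and evening separately. Subjects already keep a daily compliance record, so no extra visits or patients are needed. Make the change before unblinding.

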## Abstract

**Background:** The Coronavirus disease 2019 (COVID-19) is the largest global epidemic in recent time. Chinese medicine has been recognized by the World Health Organization as an effective treatment for COVID-19, but there is still a lack of high-quality randomized, double-blind trials using placebo as the control to support its application, which may hinder its further promotion locally and internationally.

**Objectives:** This study will evaluate the efficacy and safety of Yinqiao Powder-Maxing Ganshi Decoction with variation in relieving major symptoms of mild and moderate COVID-19 by telemedicine.

**Methods and design:** This clinical study is a randomized, double-blind, placebo-controlled trial that applies telemedicine to evaluate the efficacy and safety of Yinqiao Powder-Maxing Ganshi Decoction in the treatment of mild and moderate COVID-19. Eligible subjects will be randomly divided into either treatment or placebo groups for up to 14 days after stratification according to age (A:18–49, B:50–65) and the number of vaccinations (a: ≥3 doses, b: ≤2 doses). The treatment group will receive Yinqiao Powder-Maxing Ganshi Decoction granules along with certain variation based on their symptoms, and the placebo group will receive the same amount of placebo granules. Subjects will be prescribed different additions based on their symptoms and pathogenesis at the inclusion. The oral temperature, oximeter, result of rapid antigen test and symptom score will be recorded by subjects until they have stopped the medication. Subjects are required to have follow-up assessment by video-conference on days 7, 14 and 35. The time for the body temperature returning to normal will be used as the primary outcome.

**Discussion:** This trial will provide scientific evidence on the use of Yinqiao Powder-Maxing Ganshi Decoction for the treatment of COVID-19, and the results would help raise the awareness in Hong Kong and the international community on the use of Chinese herbal medicine for treating COVID-19.

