### Secondary outcomes

1. The recurrence rate of fever after momentary recovery: the incidence of fever recurrence (oral temperature > 37.2°C) within 24 hours after the patient’s temperature has normalized after treatment;2. The negative rate of RATs at day 14 and the negative conversion time (two successive negative RATs result with at least 24 hours interval);3. The remission rate of major symptoms at day 14 (oral temperature ≤ 37.2°C, score of cough and fatigue ≤ 1 (“None”, “Mild”, “Moderate”, “Severe” and “Very severe” were marked as 0 to 4 450 respectively), and continues 24 hours);4. Time of major symptoms remission: time from the start of treatment to symptoms remission (definition of symptoms remission: oral temperature ≤ 37.2°C, cough and fatigue score ≤ 1 and lasting at least 24 hours);5. The disappearance rates at day 14 and disappearance time of symptoms: the disappearance rates and time of individual symptoms of mild and moderate COVID-19 within 14 days (time defined as the period between starting medication and symptom disappearance); 6. The rate of patients whose oxygen saturation had gone below< 94% after intake of drugIMP, measured at day 14;7. Incidence of the progression to severe or critical illness during the trial;8. All-cause mortality at the 21st day after stopping the medication;9. Utilization rates of antipyretic, Paxlovid and molnupiravir within 14 days and the total dosage(s) of the drug(s) used.

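### The mortality window and per-protocol membership both hang on a stop date that depends on recovery; count deaths to day 35 for everyone and keep per protocol supportive

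*Protocol article*

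**What the plan says.** **Stop date.** The Study medications section sets the course at "14 days at maximum or until patients get negative RAT results on two successive days and the major symptoms subside". The next sentence adds: "The actual duration is determined by the patient according to their own condition".

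**Mortality.** The eighth secondary outcome is "All-cause mortality at the 21st day after stopping the medication", and the Assessment section uses the same timing. Separately, the follow-up section gives every subject a final video contact on day 35 (±1 day).

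**Per protocol.** The Statistical analysis section gives two routes into the set and asks for at least 85% intake compliance. One route is completing the full course, whether or not the subject has recovered. The other is for early stoppers and is tied to recovery: "if they stop until getting negative RAT results on two successive days and the major symptoms subside". The compliance denominator is the daily packs times the days on drug for a subject who stopped on the criteria, and "daily dose x 14 for all other cases".

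**End of recording.** The Abstract says the daily measurements "will be recorded by subjects until they have stopped the medication". The Assessment section says: "Subjects are required to measure the temperature until day 14 or on the day when the temperature has remained normal for 24 h", whichever comes later, and has parallel rules for antigen tests and oximetry. The follow-up section gives days 0 to 14 with a whichever-is-later clause. Table 1 gives 14 days or until recovery.

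**The concern.** The stop date is a post-randomisation event driven largely by the outcomes under study: antigen conversion and remission of fever, cough and fatigue. A definition anchored to it inherits that dependence.

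For mortality, a faster recovery shortens the observation time counted from the start of treatment. If the active granules speed recovery, that arm is watched for less time, and a death between the end of a short window and day 35 counts for a slow recoverer but not for a fast one.

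For the per-protocol set, two subjects with the same intake can be classified differently only because one converted and remitted and the other did not. Conversion and remission are themselves secondary outcomes, so a comparison within that set is partly selected on efficacy results.

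**Working it through.** **Inputs.** From the Statistical analysis section: an 85% threshold, 4 packs a day in both worked examples, and a denominator of days on drug or 14. From the Study medications section: a maximum of 14 days. From Secondary outcomes: stop date plus 21 days. From the follow-up section: a day 35 contact for all.

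**1. The plan's own figures.** Compliance = packs taken / (packs per day × denominator days).
- Stop on the criteria after 8 days with 30 packs: 30 / (4 × 8) = 93.75%. Agrees.
- Stop for an adverse event with 12 packs: 12 / (4 × 14) = 21.43%. Agrees.

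**2. Same intake, different outcome.** Both subjects take 4 packs a day for 5 days, 20 packs in all, then stop.
- Recovery criteria met: 20 / (4 × 5) = 100%, per protocol.
- Criteria not met, for example fever gone but antigen test still positive: 20 / (4 × 14) = 35.7%, not per protocol, even if the primary outcome was fully observed.

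**3. Who is excluded.** A non-recovered subject needs 0.85 × 56 = 47.6 packs, so 48.
- 11 full days: 44/56 = 78.6%, out.
- 12 full days: 48/56 = 85.7%, in.
- 14 full days: 56/56 = 100%, in by the maximum-dose route without recovery.

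**4. Mortality window.** End = stop day + 21.
- Stop on day 5: 5 + 21 = day 26.
- Stop on day 14: 14 + 21 = day 35, nine days later.
- Over stops after 2 to 14 days of dosing, the window ends between about day 22 and day 35. Each figure shifts by one day according to whether the stop is counted from the last dosing day, because dosing starts on day 0.
- The longest window ends at day 35, so the planned last contact covers all of them, apart from its ±1 day tolerance.

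**5. Can the per-protocol rule bias a comparison between arms?** This is an illustration on assumed inputs, not on document figures. There is no true effect. Time to meeting the recovery criteria follows a gamma distribution (shape 4, mean 7 days) rounded up to whole days and capped at 14, and subjects stop before recovery at a constant daily rate.

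| Daily early stopping, arm A vs B | Per-protocol share, A vs B | All-randomised difference (A − B) | Per-protocol difference (A − B) |
|---|---|---|---|
| 3% vs 3% | 83.1% vs 83.0% | 0.005 days | 0.001 days |
| 6% vs 2% | 69.2% vs 88.3% | 0.008 days | −0.361 days |

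Equal early stopping gives no difference. Unequal stopping makes the arm with more of it look about 0.36 days faster, while the all-randomised difference stays near 0. The 0.36 days is on a full-recovery time scale with an assumed SD of √4 × 1.75 = 3.5 days. It should not be set directly against the 0.5-day fever difference (SD 0.7) in the sample size section.

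**The case against.** The strongest reply is that the two denominators follow the treatment rule. A subject who stops on the criteria did what was asked; one who stops while still antigen-positive did not. Every per-protocol set conditions on events after randomisation, and a window of 21 days after the last dose is a recognised way to define post-treatment follow-up. Mortality is one of nine secondary outcomes in 96 subjects aged 18 to 65 with major comorbidities excluded. Most of this stands as a limit on importance. It does not remove the dependence on outcome: the mortality window is explicitly individual, and the set is still selected partly on secondary outcomes.

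Three stronger readings are tempting, and the document does not support them.

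- *Treatment failures drop out of the analysis.* Only non-recovered subjects who stop before about 12 full days of doses leave the set; those who complete the course stay.
- *The main comparison is biased.* No section assigns the per-protocol set to the primary analysis, and naming an all-randomised set is commonly left to the full protocol or SAP. Its absence from an article is no finding.
- *Day 14 data will be missing for early stoppers.* That follows only from the Abstract. The Assessment section keeps temperature, antigen tests and oximetry going to day 14 or later.

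The two sentences on treatment duration may also be compatible, if the second only means that patients apply the criteria to their own readings at home. The wording leaves this open, and the per-protocol rule turns on it.

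**Conclusion.** The point holds in a limited form. Two stated definitions depend on a recovery-driven stop date.

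- **Mortality:** windows differ by about nine days between a day 5 and a day 14 stop, and by about 12 days over the range worked above. The practical effect is probably small. That few deaths will occur is an inference from the eligibility criteria; the article gives no expected number.
- **Per protocol:** at equal intake, membership turns on antigen conversion and symptom remission for anyone with fewer than 48 of 56 packs (at 4 packs a day). Bias between arms requires early stopping before recovery to differ by arm; the 0.36-day figure rests entirely on the assumed 6% against 2% daily rates and the assumed recovery distribution.

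The conflict over the end of recording is a matter of wording in the Abstract and Table 1. Nothing here shows bias in the primary comparison.

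**What to change.** 1. Define the mortality outcome as all-cause death by day 35 for every randomised subject. The day 35 contact is already planned, and the Assessment section already allows confirmation through related persons or hospital records, which covers a contact made a day early.
2. State that efficacy is compared in all randomised subjects as randomised, with the per-protocol analysis supportive only. If the full protocol or SAP already says so, check that it agrees with the article.
3. Reconcile the two sentences on treatment duration in Study medications with the per-protocol rule, so that it is clear which stops count as following the plan. Which stopping rule applies is for the investigators.
4. Do not simply replace the 14-day denominator with days to any permitted stop. A subject who quits after 2 days with 8 packs would score 8 / (4 × 2) = 100%. Such a change is safe only if the reconciled rule prevents this.
5. Align the Abstract and Table 1 with the follow-up and Assessment sections on when daily recording ends.

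The cost is definition wording. No new visit, diary or measurement is needed.
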